**4. Rationale and objectives**

a) *Specific immunity to HIV and intermittent therapy*

Highly active anti-retroviral therapy (HAART) has reduced to the incidence of AIDS-defining diseases by approximately 85% [1]. Nevertheless it entails an indefinite treatment with at least three drugs and therefore implies discomfort, undesirable side-effects and high cost. Until now, attempts to stop anti-retroviral treatment (ART) have failed. Even in patients whose VL has remained undetectable for months, withdrawal from treatment has invariably been followed by rebound in VL within a few weeks [2,3]. The rebound of VL probably begins in reservoirs in latently-infected lymphocytes [4].

Although HIV destroys the immune system in most patients, a small group of patients known as long-term non-progressors (LTNP) apparently tolerate the infection for many years with few effects. In these patients, CD4 cells stay within the normal range, and VL is very low or undetectable. Most LTNPs have good and persistent lymphocytic cytotoxic response to HIV [5-8]. Nevertheless this response is transitory in non-LTNP patients, allowing the continued proliferation of the HIV infection that leads eventually to immunosuppression [9].

Preliminary data indicate that it could be possible to induce cytotoxic T cells (CTL) in patients who otherwise would progress towards immunodeficiency and that these patients control viral proliferation after stopping treatment:

- Patients treated very promptly post-infection (during the primary infection or shortly after) develop a powerful and lasting cytotoxic response to HIV [10].

- One case study reports of two patients with bad adherence to therapy who stopped treatment, causing a rebound in VL. They later resumed treatment for different lengths of time before finally withdrawing from treatment indefinitely. In both cases the VL remained undetectable for 14 and 21 months without ART. In both cases, patients presented a good and ample cytotoxic response to HIV that was probably strengthened by the rebound in VL during the first interaction in treatment. Cytotoxic response was evaluated whilst the patient was out of treatment, and it continued to remain high [11].

- Another patient treated with DDI, hydroxyurea and indinavir stopped the treatment and presented a rebound in viremia. The patient went back into treatment, after which VL decreased; treatment was then stopped again. Viremia did not rebound and remained at the same level for more than one year without treatment. The patient presented good cytotoxic response to HIV [12].

- Three patients with stable viremia were treated with a combination containing hydroxyurea under the following schedule: three weeks of treatment, one week of interruption followed by two cycles of three months therapy with interruption and resumption of treatment once VL went back up (>5,000 copies/mL). VL became undetectable (<400 copies/mL) after each return to treatment. The relapse-free intervals increased by seven days after the first interruption and went up to 37 days after the third interruption [12].

-*Rhesus macaques* infected with SIV/Mac251 (basal viremia: 200,000 copies/mL, 500,000 copies/mL and 1.1 million copies/mL) were treated with hydroxyurea, DDI and a derivative of adefovir following an intermittent schedule (two cycles of three weeks of treatment followed by interruption). SIV was allowed to rebound to >5,000 copies/mL. Although VL rebounded, in three cases it was controlled and stabilised to a low level of viremia in the absence of treatment. This level was >5,000 copies/mL and was maintained for six weeks during the first interruption and reduced to <200 copies/mL at the lowest and maintained for ten weeks during the third interruption. Two of the monkeys continued without relapse after four and six months respectively [12].

The intermittent interruption of treatment is associated with a strengthening of the cytotoxic response to HIV that can contribute to a prolonged suppression of VL when treatment is withdrawn.

1. *Acute suspension of treatment is acceptably safe*

Chronic exposure to sub-therapeutic levels of anti-retrovirals can promote resistant mutations and lead to a loss in efficacy. Nevertheless the abrupt interruption of treatment does not seem to be associated with the formation of resistance. In the cases of interruption of the treatment, viral proliferation originates in viral reservoirs in non-activated T lymphocytes. Numerous studies have demonstrated that the virus remaining in the reservoirs is sensitive to ART [13].

Neumann et al. and Garcia et al. have reported triple treatment interruption therapies, with follow-up in patients until VL rebounded and reached stable levels, before returning to ART. In the 23 patients, control of VL was at least as quick during the second round of treatment as it was in the first round. All patients had a VL of <200 copies/mL at six weeks of the second course of treatment.

1. *Effects of IL-2 administration*

Numerous studies have looked at combining ART with three or more anti-retroviral drugs with cycles of IL-2 administered during five days in high (18 million UI/day) or intermediate (3-6 million UI/day) doses via i.v. or s.c. every eight weeks (14-23). This approach has been used in advanced patients (with CD4+ lymphocyte counts <200-500 cell/µL) with the aim of increasing the number of CD4+ lymphocytes, improving other immunological parameters and reducing the apoptosis of T lymphocytes. In addition, observations have shown that the concurrent administration of elevated doses of IL-2 and ART reduces the pool of latent CD4+ lymphocytes that contain the DNA of integrated HIV-1 (21). Nevertheless, when ART is stopped, there is a fast rebound of HIV-1 plasma VL (22). On the other hand, high or intermediate IL-2 doses have numerous side-effects, mainly when administered by i.v. (24). This toxicity is dose-dependent. There are no adverse effects when it is administered in low doses. In this sense, exceptional adverse effects were noted in a study of patients with neoplasia related to HIV-1 infection receiving low doses of IL-2 (0.5-1.2 million UI/day) for 3 months but, on the other hand, there were no observations of opportunistic infections or increases in HIV-1 plasma VL, embodying an immunological improvement of Th1 cell response (24).

The aim of administering very low doses of IL-2 to patients with primary HIV-1 infection treated from the beginning of the acute infection is based on a study by the group of [name]. In this study, very low doses of IL-2 were administered during six months via s.c. in asymptomatic patients with a chronic HIV-1 infection receiving single-agent ART and having a relatively high HIV-1 plasma VL. The patients did not suffer side-effects and were able to self-administer IL-2 and to maintain daily activities (31). In addition, it was shown that with this dose of IL-2, a series of immunological benefits were to be obtained: 1) a qualitative improvement in the immune system, measured by delayed hypersensitivity antigen skin memory tests; 2) an increase in CD4+ lymphocytes; 3) an absence of significant changes in HIV-1 plasma VL; and 4) an absence of measurable increases of pro-inflammatory plasma cytokines (TNF-a, IFN-g, GM-CSF) (31). The maximum non-toxic therapeutic dose over six months was obtained with the daily s.c. administration of 187,000-250,000 unit/m2/day. Peak plasma IL-2 levels were 22 pM, sufficient to saturate ³70% of high affinity IL-2 receivers in T, B and NK cells, but only 2% of low affinity IL-2 receivers. This study also demonstrated the effectiveness of the administration of a single dose of 125,000 units/m2/day (25). So it seems this very low, side-effect-free IL-2 dose is an ideal addition to ART to expand selectively *in vivo* high affinity IL-2 receivers in CD4+ and CD8+ lymphocytes once activated with a specific antigenic stimulus, in this case, HIV-1 during the period of ART interruption. This is possible as CD4+ lymphocytes have T-cell receivers capable of recognising the antigens in the antigen-presenting cells. On the basis of this data, we think that combining IL-2 with structured interruptions of ART could be feasible and could expand the specific HIV response of CD4+ and CD8+ lymphocytes once activated during the rebound of VL and to allow a control of the HIV-1 viral replication after the suspension of ART after the fourth cycle. This hypothesis was recently verified in an experiment on higher primates, in which the administration of IL-2-Ig, which is functionally more efficient than the natural IL-2, significantly increased the cellular and humoral immune response of animals vaccinated with HIV-1 and SIV DNA (26).

General aim:

To evaluate the virological response and the specific cytotoxic response to HIV, the point of stabilisation of viremia after fourth cycle of interruption of anti-retroviral treatment (ART), and the proportion of patients who do not require ART at the end of study following the administration of subcutaneous, low doses of IL-2.

Specific aims:

- To determine the proportion of patients with VL increases at least three times greater than the baseline value (prior to ART) (corresponding approximately to an increase of 0.5 log).
- To determine the proportion of patients with specific cytotoxic response to HIV
- Compare the level of viremia stabilisation at the point of stopping ART by comparing viremia at the end of the fourth cycle and at the end of the study with pre-HAART viremia.
- Determine the proportion of patients not requiring ART at the end of the study.

***

**5. Trial type and design.**

1. Phase of development:

Phase III

1. Description of the randomisation process:

Not applicable as the trial is non-comparative.

c) Type of control and design:

A single-centre, non-comparative, prospective, open-label, clinical pilot study.

d) Blinding methods:

Not applicable as this is an open-label trial.

e) Follow-up period:

Two years

***

**6. Subject selection**

a) Inclusion criteria:

The trial will include patients of both sexes:

1. with diagnosed HIV-1 infection;
2. aged 18 years or older;
3. treated with HAART anti-retroviral treatment (composed of two analogues non-nucleoside reverse transcriptase inhibitors plus a protease inhibitor) since primary infection;
4. plasma viral load <50 copies/mL (Roche Monitor Assay) for at least eight months;
5. CD4 lymphocyte count consistently >500 cells/L (prior to stopping treatment); and
6. who, having been appropriately informed, have granted written consent to take part in the study and to be subjected to tests and examinations that it entails.

b) Exclusion criteria:

1. Patients who have responded suitably to the initial anti-retroviral treatment;
2. patients who have at some time taken nevirapine or efavirenz; and
3. women who are pregnant or lactating, or who intend to become pregnant during the period of the study.

c) Predicted number of subjects:

There will be eight outpatients.

d) Methods for calculating the sample size and data used:

As this is a pilot study, there is no way of knowing what kind of data will be produced in response to this treatment in this subtype of patients with primary HIV infection. The results of this study will allow the calculation of the sample necessary to create a comparison with an appropriate statistical basis.

e) Discontinuation criteria and anticipated analysis of withdrawals and discontinuations:

Patients will be able to leave the study at any time without having to give explanations. Nevertheless, the causes for discontinuation will be collected and recorded in the data collection notebook (DCN).

The researcher will also be able to withdraw patients from the study for reasons of inefficiency, adverse events or patient benefit. The reason for withdrawal will be recorded in the DCN.

All patients who, having been assigned to a treatment group, discontinue the treatment under study or who are withdrawn for any cause will be included in an “intention-to-treat” analysis.

The patients who fail to attend appointments (loss of follow-up) will be considered for the analysis until the moment at which the loss takes place.

f) Dealing with pre-randomisation losses:

Patients who fulfil selection criteria but who, for whatever reason, are not included in one of the treatment groups will be recorded as appropriate (personal, demographic data, etc.), but they will not be included in the analysis.

g) Approximate duration of enrolment:

A period of two months is planned to recruit eight patients with the described characteristics.

***

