1.9. Phase of the trial: Phase III

1.10. Primary goal:

To evaluate the virological response, the specific cytotoxic response to HIV and the point of stabilisation of viremia after the fourth cycle of interruption of anti-retroviral treatment (ART), and the proportion of patients who do not require ART at the end of study following the administration of subcutaneous, low doses of IL-2.

1.11. Experimental design:

A single-centre, non-comparative, prospective, open-label, clinical pilot study.

1.12. Disease being studied:

HIV-1 infection.

1.13. Main evaluation variables:

The proportion of patients presenting plasma viral load (VL) three times greater than the base value (prior to ART), or VL >20 copies/mL where base VL <10 copies/mL;

The proportion of patients with good cytotoxic response after the fourth cycle compared with the beginning of the treatment;

The proportion of patients having been administered with IL-2 not requiring ART at the end of the study. (>350 CD4 cells or VL <55,000 copies/mL).

1.14. Test population:

The study will include eight HIV infected, outpatients having begun highly active antiretroviral treatment (HAART) during primary infection.

1. Duration of the treatment:

The treatment will be administered daily from the first interruption of ART with a subcutaneous dose of 125,000 mIU/m2 for six weeks. After completing four cycles of six weeks, the treatment with IL-2 will be stopped. Patient follow-up will be conducted for two years.

1.16. Schedule and anticipated date of conclusion:

The aim is to start the trial, provided authorisation has been obtained, in November 2001. The recruitment period will last two months, and the follow-up will last two years. The aim is to finish the study in December 2003.

***

**2. Contents** page

1. Summary 2

2. Contents 5

3. General information 6

4. Rationale and objectives 8

5. Trial type and design 12

6. Subject selection 13

7. Description of the treatment 15

8. Trial development and response evaluation 17

9. Adverse events 19

10. Ethical aspects 21

11. Practical considerations 22

12. Statistical analysis 23

13. References 25

Annexes:

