**7. Description of the treatment**

Patients will stop antiretroviral treatment for eight weeks and will return to it for eight to twelve additional weeks with the addition of interleukin-2 for six weeks.

This process will be repeated four times. Upon finishing the four cycles, treatment with IL-2 and ART will be suspended unless there has been evidence of viral replication to the point that viral load (VL) reaches a stable level. (Definition of point stabilization: equal VL in three sequential determinations separated by at least three weeks)

a) Doses, intervals, method and form of administration and duration

Interleukin-2 (IL-2), 125,000 units/m2/day, subcutaneously, for six weeks

b) Criteria for modifying the protocol during the trial:

 INTOLERANCE/TOXICITY

Interleukin-2: the tolerance of the medication will be evaluated at each visit with a view to its suspension in cases where the severity or intensity of adverse effects so prescribe.

 SAFETY MEASURES

Because of concerns over an eventual appearance of resistance and a loss of antiretroviral treatment efficacy, various measures have been designed to ensure that intermittent therapy will be immediately discontinued in case there is a failure to:

- Analyse the response to treatment in the weeks leading up to each interruption. VL will be measured at seven weeks after restarting treatment in each cycle. The study will be stopped if more than two favourable responding patients reach VL <50 copies/mL.

- The study will only be interrupted between weeks 64 to 80 in those patients who show lowered VL after the third interruption compared with the first interruption.

- ART will be started in patients with CD4+ lymphocyte count <350 cells/µL or with an HIV-1 plasma VL >55,000 copies/mL in two consecutive determinations (27). In asymptomatic patients with CD4+ lymphocyte count between 350-500 cells/µL and/or VL between the previous levels, the evaluation of resuming ART will be done on an individual basis.

- There will be a safety commission.

c) Concomitant medications:

Any concomitant medication will be reflected appropriately in the DCN (detailing the product, dose, administration method, day of administration, reason for the treatment, etc.).

1. Salvage medication:

ART will be started in patients with CD4+ lymphocyte count <350 cells/µL or with an HIV-1 plasma VL >55,000 copies/mL in two consecutive determinations (27).

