**12. Statistical analysis**

a) Statistical tests:

- Descriptive analysis:

The descriptive analysis will include variables referring to demographic data and clinical events related to the sample as well as adverse reactions in terms of absolute and relative frequency, means and standard deviations, medians and ranges.

*Indications for antiretroviral treatment*

Spanish recommendations for ART (27) prescribe that it should not be given to patients who are asymptomatic with CD4+ lymphocyte cell count <500 µg/L and a viral load <10,000 copies/mL. The proportion of patients presenting both criteria will be determined at two points: 1) when VL reaches the set-point following the last withdrawal from treatment; and 2) at the end of the study (week 120-136).

- Comparative Analysis

*1) Increase in plasma VL in the* ***eighth*** *week following withdrawal, and 2) proportion of patients with cytotoxic response to HIV.*

- Comparison will be made between cycles one, two, three and four.

An increase in VL is defined as being at least three times greater than the baseline (prior to ART) (corresponding approximately to an increase of 0.5 log).

- In patients with a VL <10 copies/mL (undetectable), an increase will be considered as being any value >20 copies/mL after two weeks since the interruption of treatment.

- A more sensitive analysis will compare the second, third and fourth cycles with the first cycle, for each patient, as paired data. McNemar’s test will be used to compare discordant results: i.e., N pairs with a higher value for the first cycle and a lower value for the fourth cycle, with the N pairs from the opposite situation. The same considerations will be applied to the evaluation of the cytotoxic capacity and function of CD4 *helper* lymphocytes, which will be recorded as positive vs. negative or good vs. weak versus according to the stimulation index.

*2) Analysis of VL increase time above 5,000 copies/mL.*

- The treatment will be stopped in weeks 64-80, if viremia in week 56 is less than in week eight.

- The increase time will be compared (measurement history) with that of other groups (see references 2 and 3)

3) *Multivariant analysis*

A ‘response’ is defined as the lack of a rebound or the absence of indications for ART on multiple occasions following the interruption of treatment.

The indicating response factors will be evaluated by means of multiple regression analysis, and will include:

- CD4 count before ART,

- VL before HAART,

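### The CD4 thresholds are not on one scale: the entry floor is in cells/L, one analysis limit is in µg/L, and the 350 outcome limit has no volume unit

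*Protocol*

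**What the plan says.** CD4 thresholds appear in five places in the Protocol:

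- **Section 4, Effects of IL-2 administration** describes earlier IL-2 studies in patients with "CD4+ lymphocyte counts <200-500 cell/µL".
- **Section 6 a), inclusion criterion 5** sets the entry floor: "CD4 lymphocyte count consistently >500 cells/L (prior to stopping treatment); and". No other inclusion or exclusion criterion sets a CD4 limit.
- **Section 7 b), Safety measures** gives the ART-start rule: "ART will be started in patients with CD4+ lymphocyte count <350 cells/µL or with an HIV-1 plasma VL >55,000 copies/mL in two consecutive determinations (27". It is repeated in the salvage paragraph of Section 7. An individual-review band follows: "In asymptomatic patients with CD4+ lymphocyte count between 350-500 cells/µL and/or VL between the previous levels".
- **Section 12 a), Indications for antiretroviral treatment** says that national recommendations advise against ART in asymptomatic patients with "CD4+ lymphocyte cell count <500 µg/L and a viral load <10,000 copies/mL". It plans to report the proportion of patients meeting both criteria at the set-point after the last withdrawal and at the end of the study.
- **Summary item 1.13** defines not requiring ART at the end of the study by ">350 CD4 cells or VL <55,000 copies/mL".

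**The concern.** The same laboratory quantity governs who may enter, when ART is started, and two outcome proportions. It is given in cells/µL (Sections 4 and 7), in cells/L (Section 6), in µg/L (Section 12), and with no volume at all (Summary item 1.13).

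The intervention includes withdrawal of ART, so criterion 5 is the only CD4 check at the point of eligibility. A criterion that no enrolment could breach gives a supervisor or inspector nothing to verify against. The Section 12 limit defines a planned descriptive outcome. A threshold in an impossible unit, and one that also seems to run against the Section 7 rule, leaves that outcome open to different scoring by different analysts.

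**Working it through.** **Inputs.** Entry floor: 500 cells/L (Section 6). ART-start limit: 350 cells/µL (Section 7). Review band: 350-500 cells/µL (Section 7). Conversion: 1 L = 1,000,000 µL. The Protocol derives no figure from criterion 5, so there is no calculation of its own to reproduce.

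**Step 1: the entry floor on the Section 7 scale.**
500 cells/L ÷ 1,000,000 µL/L = 0.0005 cells/µL.

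**Step 2: the ART-start limit on the Section 6 scale.**
350 cells/µL × 1,000,000 = 350,000,000 cells/L.
350,000,000 ÷ 500 = 700,000. The ART-start limit is therefore 700,000 times the written entry floor. If both were per µL, the floor would lie above the limit by 500 ÷ 350 = about 1.4-fold. The gap between the units is 1,000,000. The gap between these two thresholds is 700,000.

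**Step 3: who passes under each reading.**

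| CD4 (cells/µL) | Passes >500 cells/L | Passes >500 cells/µL | Below 350 cells/µL |
|---|---|---|---|
| 1 | yes | no | yes |
| 200 | yes | no | yes |
| 349 | yes | no | yes |
| 350 | yes | no | no |
| 500 | yes | no | no |
| 501 | yes | yes | no |

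Read literally, every row is eligible, including counts at which Section 7 starts ART. Read per µL, the floor begins exactly where the 350-500 band ends. That fit is internal evidence that cells/µL was meant.

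**Step 4: the Section 12 limit.** µg/L is mass per volume, so no conversion turns it into a cell count. Correcting the unit alone does not settle the sentence. Suppose the 500 is taken as cells/µL:

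- A patient at 349 cells/µL with a viral load under 10,000 copies/mL meets both Section 12 criteria and is counted as having no indication for ART. Section 7 has "ART will be started in patients with CD4+ lymphocyte count <350 cells/µL".
- A patient at 501 cells/µL with the same viral load does not meet both Section 12 criteria, although Section 7 gives no CD4 reason to start ART.

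The two passages run in opposite directions on CD4. They also use different viral-load limits (10,000 against 55,000 copies/mL).

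**Step 5: Summary item 1.13.** The figure 350 matches the Section 7 limit numerically, but the volume is left to be inferred.

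**The case against.** **A lost character.** The text was extracted from a file, and cells/L differs from cells/µL by one symbol. Some symbols in Section 4 are visibly damaged. This cannot be fully excluded for criterion 5. However, the damage in Section 4 looks like substitution rather than deletion, and the micro sign survives in Sections 4, 7 and 12. In Section 12 the micro sign is present and the unit is still impossible, so that part stands on any reading.

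**Nobody would apply it literally.** This objection largely holds. A floor of 0.0005 cells/µL is not one that an HIV team could take as intended, and every other CD4 threshold with a valid volume unit is per µL. That the criterion excludes nobody is a statement about the text, not a forecast of enrolment.

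**Stronger readings.** A reader might go further than the documents allow in three ways:

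- *Patients below the ART-start limit will be enrolled, each being 12.5% of the sample (1 ÷ 8).* This presumes that someone applies the literal limit, and nothing in the Protocol suggests that. CD4 is also scheduled at week 0, and the Section 7 rule is in a usable unit.
- *Such a patient fails the outcome from day 0.* The variable is scored at the end of the study, and Summary item 1.13 joins its two parts with an or, so a low CD4 count alone does not decide it.
- *The 700,000-fold ratio measures harm.* It only restates the missing prefix.

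**Conclusion.** The inconsistency is real, but the correction is minor. As written, the only CD4 eligibility limit is 0.0005 cells/µL and excludes no measurable count. One analysis limit is in a unit that cannot apply to cells, and one outcome limit has no volume.

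The likely effect on actual enrolment is small. This rests on two assumptions: that the extracted text of criterion 5 is faithful, and that the site would read it as cells/µL. If the first fails, the criterion 5 part falls away, and the points on Section 12 and Summary item 1.13 remain.

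No sample size, test or interim rule in the Protocol uses criterion 5, so no computed result changes. The more substantive residue is in Section 12. There the reported proportion depends on a CD4 limit that conflicts in direction with Section 7 even after its unit is corrected.

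**What to change.** 1. State the CD4 thresholds in Summary item 1.13, Section 6 criterion 5, Section 7 and Section 12 in one named unit. Sections 4 and 7 already use cells/µL.
2. Reconcile the Section 12 sentence with the Section 7 ART-start rule, both in the direction of the CD4 limit and in the viral-load value. The investigators should check it against the recommendations they cite, so that the descriptive outcome and the treatment rule agree or their difference is explained. Which clinical limit is right is for them to settle.

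The cost is a few lines in one amendment. The design, the eight-patient sample and the visit schedule do not change. The second item also needs a short clinical check of the cited source.

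### Section 6e promises intention-to-treat but counts lost patients only until loss, and it lets patients leave the study for lack of efficacy with no later values, so the fourth-cycle and end-of-study proportions have no consistent denominator

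*Protocol*

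**What the plan says.** Four statements matter, the first three of them in Protocol section 6e.

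- **Withdrawal by the investigator:** "The researcher will also be able to withdraw patients from the study for reasons of inefficiency, adverse events or patient benefit". No criterion is given. I read the word for the first reason as lack of efficacy, probably a translation matter. The withdrawal is from the study, not only from the study treatment.
- **Withdrawn or discontinued patients:** those who stop treatment or are "withdrawn for any cause will be included in an “intention-to-treat” analysis".
- **Lost patients:** those who miss appointments "will be considered for the analysis until the moment at which the loss takes place".
- **Where the rules are applied:** the main variables in section 8a include viremia at the end of the fourth cycle and at the end of the study, and the share of patients who then need no ART. Section 12a places the end of the study at week 120-136. For VL increase and cytotoxic response it says "Comparison will be made between cycles one, two, three and four", followed by a within-patient comparison of cycles two to four with cycle one by McNemar's test.

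The sample is fixed in section 6c: "There will be eight outpatients". No dropout rate is given.

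**The concern.** There are two linked problems.

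**The rules conflict.** An intention-to-treat proportion at a late time point needs every patient in the denominator. A rule that considers a patient only up to the time of loss takes that patient out of every later denominator. For a proportion measured in cycle four or at week 120-136, both rules cannot hold for the same patient.

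**Withdrawal can depend on the outcome.** The trial is open-label and has one arm, so the investigator sees the VL results when deciding. Lack of efficacy is what the VL-increase and need-for-ART variables measure. A patient who leaves the study for that reason is included in the analysis by name but may have nothing to include. No later VL, CD4 or cytotoxic result need exist, and section 6e gives no score in its place.

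At stake are the late proportions, which carry the trial's message on viral control off ART. Section 6d also intends the results to size a later comparative study, so a distorted proportion would carry forward.

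**Working it through.** **Is there a figure to reproduce?** No. Section 6d gives no calculation: "As this is a pilot study, there is no way of knowing what kind of data will be produced in response to this treatment". What follows illustrates the size. The success and dropout counts are assumptions; only N = 8 comes from the protocol.

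**Step 1: the rules side by side, for a patient with no cycle-four or end-of-study value.**

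| Reason for no value | Rule in section 6e | In the late denominator? | Score |
|---|---|---|---|
| Withdrawn for lack of efficacy | intention-to-treat | yes, by the wording | none stated |
| Lost to follow-up | counted until loss | not if counted only until loss | none |

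**Step 2: effect on a proportion.** Let s be the successes observed and k the patients not counted. The all-patients estimate is s/8 and the available-patients estimate is s/(8 − k). Intervals are exact (Clopper-Pearson) 95%.

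| Assumed case | Estimate | 95% CI |
|---|---|---|
| 3 successes, all 8 counted | 3/8 = 37.5% | 8.5-75.5% |
| 3 successes, 1 non-success not counted | 3/7 = 42.9% | 9.9-81.6% |
| 3 successes, 2 non-successes not counted | 3/6 = 50.0% | 11.8-88.2% |
| 1 of the 3 successes lost and not counted | 2/7 = 28.6% | 3.7-71.0% |

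Uncounted non-successes raise the estimate by 42.9 − 37.5 = 5.4 points for the first and 50.0 − 42.9 = 7.1 points for the second. One lost success lowers it by 37.5 − 28.6 = 8.9 points. The direction depends on who is missing.

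**Step 3: effect on the paired comparison.** McNemar's test needs both values of a pair, so a patient without a cycle-four value adds nothing to cycle four versus cycle one. With n complete pairs, all discordant in one direction, the smallest two-sided exact p is 2 × 0.5^n:

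- n = 8: 0.0078
- n = 7: 0.0156
- n = 6: 0.031
- n = 5: 0.0625

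The protocol states no significance level. At an assumed two-sided 0.05, three missing patients put significance out of reach whatever the data show.

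**The case against.** **Withdrawn failures are expressly kept.** Section 6e includes patients withdrawn for any cause, and lack of efficacy is a cause. This stands. A reader might infer that failing patients drop out of the later denominators and so produce a falling rebound rate across cycles. The text does not say so.

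**Lost patients need not be failures.** This also stands. The until-loss rule covers missed appointments, and step 2 shows that a lost success moves the estimate down.

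**The paired analysis would not show false improvement.** If no patient's status changes between cycles, there are no discordant pairs, and removing patients creates none. Missing patients then cost pairs but do not by themselves produce a signal of viral control. A misleading trend could arise only in the unpaired proportions by cycle, and only if withdrawn failures went unscored.

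**Failures have another documented route.** Section 7 has ART started when its CD4 or VL criterion is met, and has that medication recorded for the whole of follow-up. Such patients have an outcome for the need-for-ART variable and are not removed by that rule. This narrows the problem to patients who also leave the study. It also shows that the protocol expects to follow failures, which sits poorly with ending their participation under 6e.

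**Scoring of missing values belongs in the SAP.** This is partly right, since detailed imputation can go there. But the until-loss rule is an analysis rule already stated in the protocol, and an SAP that kept all eight patients would contradict it. Nor can an SAP recover measurements that stopped because the patient left the study.

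**Data up to loss are ordinarily used.** That is true for repeated measures and for the time to VL above 5,000 copies/mL in section 12a. It does not settle a proportion at a fixed late time.

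**Conclusion.** The point holds in a limited form. For the fourth-cycle and end-of-study proportions, the until-loss rule cannot be reconciled with intention-to-treat. Separately, withdrawal from the study for lack of efficacy can leave failures nominally in the analysis but without later values or a stated score.

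The documents do not support the stronger conclusion that the plan removes failures and so favours the treatment. Losses can bias the result either way. The bias is favourable only if withdrawn failures go unscored.

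On the assumed counts, the same trial could report 29%, 37.5% or 50% depending on who is missing and how they are counted. The exact intervals overlap widely, as they must with eight patients, so the issue is an ambiguous estimate rather than a reversed conclusion. It should be corrected, but it does not undermine the pilot as a whole.

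**What to change.** 1. In section 6e, separate stopping study treatment from leaving follow-up. The investigator's discretion over treatment stays as it is. Patients who stop continue the VL, CD4 and cytotoxic tests already in the section 8 calendar, unless they withdraw consent.
2. For each main proportion, use all patients who began the first interruption as the denominator.
3. Count withdrawal for lack of efficacy, and loss with no later value, as failure: VL increase, requires ART, no good cytotoxic response.
4. For losses, add a best/worst-case range. For example, with three successes seen and two patients lost, report 3/8 = 37.5% (worst) to 5/8 = 62.5% (best).
5. Restrict the until-loss rule to the analysis of time to VL above 5,000 copies/mL, where it acts as censoring.

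**Cost:** a wording change, plus completing scheduled tests in patients who would otherwise have left. The proportions will be slightly less favourable, and scoring failure is conservative for losses unrelated to outcome; the range in item 4 shows by how much.
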